### 4.2 Informed Consent Process

After the consent of the daycare centre's management and sponsoring institution to implementation of the study has been obtained, all children's families and all childcare workers will receive information material and informed consent forms pertaining to the intended study and the specific module to be carried out in their daycare centre. The documents will be distributed by e-mail by the daycare centre's management. Parents/guardians and childcare workers will be asked for their consent to study participation separately for the following parts of the study: (i) initial questionnaire (paper questionnaire) (ii) further questionnaires (including pseudonymised electronic questionnaires, children interviews), (iii) respiratory sample collection, (iv) blood sampling, (v) guided interviews in a sample of participants. The number of parents/guardians and childcare workers declining participation in any part of the study from the outset will be recorded; if possible, they will be asked to state the reasons for their complete denial of consent. For respiratory sample collection and blood sampling, the consent of both parents/guardians will be required, for the other study parts (questionnaires and interviews) the consent of one parent/guardian will be sufficient. Parents/guardians will be asked to print the informed consent forms and hand in the completed forms in a sealed envelope at the daycare centre. If required, printed versions of the informed consent forms can be provided at the daycare centre. Sealable envelopes pre-addressed to the central study office will also be deposited at the daycare centre for the parents/guardians.

Together with the informed consent forms, an initial basic questionnaire will be sent out. The informed consent forms will include the option to give consent separately for this part of the study, and the aim is that as many parents/guardians as possible will participate in this initial questionnaire. If consent to other study parts is denied, the initial questionnaire aims to establish the reasons. In addition, the initial questionnaire will include questions on basic sociodemographic data (e.g. age and sex of the index child, number of family/household members, parents' employment status and educational level). For non-participants (denial of consent to participation in central surveillance measures) who nonetheless have provided written consent to participation in this initial basic questionnaire, the data obtained in the initial questionnaire will be completely anonymised. The initial questionnaire will also include questions on participants' opinions regarding the pandemic (personal assessment of the dangers of SARS-CoV-2 and of the sociopolitical response to the pandemic) and their opinions on vaccinations. Persons consenting to participation in this part of the study will be asked to enclose the initial questionnaire in the envelope with the informed consent forms to be handed in at the daycare centre.

Members of the study team will transport the sealed envelopes with the consent forms and, where applicable, the initial basic questionnaires, to the central study office, where the documents will be recorded and archived. For each daycare centre, participant lists for the individual study parts will be created, and each participant will be assigned an ID number (pseudonymisation).

For these daycare centers participating in the main parts of the study, the proportion of potential participants (children, childcare workers) not participating due to missing informed consent will be recorded.

For all participants, written consent to participation in further questionnaires (including children interviews), respiratory sample collection, serological testing (blood sampling at the beginning and end of the study (cf. 6.4.3)) and in guided interviews (in a sample of participants) will be recorded.

Once a daycare centre's participation in the central monitoring measures of the study has been established, the objectives and contents of the study will be explained in child-friendly language to all children of suitable age groups participating in the respective surveillance module.

### **4.3 Questionnaires, interviews and clinical examinations**

Within this study, four alternative monitoring programmes (4.3.1) for surveillance purposes will be compared. The monitoring measures will be carried out within the same 12-week period at all participating daycare centers. Irrespective of the type of monitoring implemented in the individual daycare centers, the participating children, families and childcare workers will be asked to answer questions regarding the psychosocial implications of the respective monitoring strategy (4.3.1). The SARS-CoV-2 immune status of children and childcare workers for whom informed consent to blood sampling was obtained, in module 4 also parents/guardians and other household members, will be determined using serological testing.

#### **4.3.1 Monitoring programmes (SARS-COV-2)**

##### **4.3.1.1 Module 1: Intensive Monitoring – mid-turbinate swabs (1 centre, at least 100 children,**

2 mid-turbinate swabs per week)

All participating children and childcare workers in the selected daycare centre will be tested for SARS-CoV-2 with a mid-turbinate swab (cf. 6.4.1) twice a week (on Mondays and Thursdays). Test results will be available 24 hours after taking the swab. If a person is tested positive for SARS-CoV-2, the case module (4.3.1.8) will come into effect.

The monitoring programme will be continued for a period of 12 weeks.

4.3.1.2 Module 2: Extensive Monitoring – mid-turbinate swabs (1 centre, at least 100 children, 1 mid-turbinate swab per week)

All participating children and childcare workers in the selected daycare centre will be tested for SARS-CoV-2 with a mid-turbinate swab (cf. 6.4.1) once a week (on Wednesdays). Test results will be available 24 hours after taking the swab. If a person is tested positive for SARS-CoV-2, the case module (4.3.1.8) will come into effect.

The monitoring programme will be continued for a period of 12 weeks.

4.3.1.3 Module 3: Intensive Monitoring – saliva samples (1-3 centers, at least 175 children overall, 2 saliva samples per week)

All participating children and childcare workers in the selected daycare centers will be tested for SARS-CoV-2 using a saliva sample (cf. 6.4.2.) twice a week (on Tuesdays and Fridays). Test results will be available 24 hours after sampling. If a person is tested positive for SARS-CoV-2, the case module (4.3.1.8) will come into effect.

Children below the age of 2 years will not be included in the monitoring programme of module 3.

4.3.1.4 Module 4: Symptom-based Monitoring (4-6 centers)

The symptom-based monitoring programme is based on a strategy of testing symptomatic children and childcare workers at the daycare centers and also *symptomatic household members* of children and childcare workers in the event of *potential COVID-19 symptoms*. All household members will be informed about potential symptoms of COVID-19 using suitable information material and announcements on notice boards in the daycare centre. They will be asked to contact the central study office directly in the event of symptoms.

Symptomatic participants of module 4 will be offered the option of having a oropharyngeal swab for SARS-CoV-2 in the COVID-19 testing centre at the University Hospital Würzburg, building D20. Symptomatic participants who do not take up this offer will be asked to notify the central study office of the result of the SARS-CoV-2 test performed by third parties (e.g. general practitioner). All symptomatic persons (in the case of symptomatic children the parents/guardians) will be asked to provide information on the time of disease onset and the observed symptoms in a standardised questionnaire.

If a symptomatic child or childcare worker or a symptomatic household member of a child or childcare worker in module 4 is tested positive for SARS-CoV-2, the case module (4.3.1.8) will come into effect.

The symptom-based monitoring programme (module 4) will also include serological tests (4.3.3) and psychosocial questionnaires (4.3.2).

The monitoring programme will be continued for a period of 12 weeks.

#### 4.3.1.5 Additional offers for symptom-based testing of symptomatic children and childcare workers in modules 1-3

According to the regulations in force at present, children with infection symptoms are not allowed to attend daycare centers and symptomatic childcare workers are obliged to stay off work. This restriction will concern all study participants, irrespective of which study module the children and childcare workers are enrolled in.

According to the study protocol for module 4, symptomatic children, symptomatic childcare workers and symptomatic household members of participating children and childcare workers will be tested for SARS-CoV-2.

In modules 1-3, symptomatic children and/or childcare workers and their symptomatic household members will be offered the option to arrange an appointment for a oropharyngeal swab for SARS-CoV-2 in the COVID-19 testing centre at the University Hospital Würzburg, building D20.

Parents/guardians of children participating in modules 1-3 will be given the option to perform sample collection (mid-turbinate swabs, saliva samples) of their symptomatic children themselves.

If they do not take up either of these offers, they will be asked to notify the central study office of the result of the SARS-CoV-2 test performed by third parties (e.g. general practitioner).

All symptomatic persons (in the case of symptomatic children the parents/guardians) will be asked to provide information on the time of disease onset and the observed symptoms in a standardised questionnaire.

Medical care for symptomatic persons will not be provided within this study, but will lie in the responsibility of the participants' primary care physicians/pediatricians.

#### 4.3.1.6 Sample collection and sample processing

All staff taking swabs will be protected by an unvalved FFP2 mask or by a face shield.

The mid-turbinate swabs will be taken within the premises of the daycare centre by medically trained staff (medical students working as research assistants, practice nurses, medical technical assistants) in the presence of a pediatrician. If feasible, parents can, at a later stage of the study and after receiving practical instructions from the study team, be given the option to take the swabs themselves at home on the scheduled days and bring the samples to the daycare centre.

Only the initial saliva samples will be taken by medically trained staff within the premises of the daycare centre. During this initial sampling, parents will be instructed how to take the samples themselves. All further saliva samples will be taken by the parents at home in the morning and handed in at the daycare centre. This procedure prevents any potential spread of droplets and aerosols during sampling in the daycare centre. Only children at least 2 years of age and therefore able to give saliva samples will be included in the intensive monitoring programme based on saliva sampling.

Oropharyngeal swabs will be taken in the COVID-19 testing centre at the University Hospital Würzburg, building D20.

Processing, analysis and diagnostic interpretation of swabs/saliva samples will be carried out at the Institute of Hygiene and Microbiology and/or the Institute of Virology at the University of Würzburg. This ensures that the SARS-CoV-2 test result and diagnosis will be available and passed on to the participant within 24 hours of sample collection. In the event of a positive test result, the participant will be notified directly by telephone and the local health authorities will be informed in accordance with §7 Infection Protection Act ("Infektionsschutzgesetz") (4.3.1.8).

Remaining respiratory sample material will be stored for additional analyses which shall be carried out at a later date for logistical reasons. In these additional analyses, expected to be performed in summer 2021, multiplex PCR will be used to test for other common respiratory viruses (e.g. influenza virus, RSV, rhinovirus, other coronaviruses, adenovirus). As these additional analyses will be carried out some months after completion of the monitoring programme in the daycare centers, participants (parents/guardians) will not receive additional notification of the results of these tests.

#### 4.3.1.7 Notification of positive SARS-CoV-2 results

If symptomatic or asymptomatic children, household members or childcare workers are tested positive for SARS-CoV-2 in the diagnostic laboratory (Institute of Virology / Institute of Hygiene and Microbiology), the local health authorities will be notified in accordance with §7 Infection Protection Act ("Infektionsschutzgesetz").

In addition, in the event of a positive SARS-CoV-2 test result the participants directly concerned will be informed by one of the physicians at the central study office and will receive standardised written information.

#### 4.3.1.8 Case Module

In the event that a child, household member or childcare worker is tested positive for SARS-CoV-2, the diagnostic laboratory will notify the local health authorities in accordance with §7 Infection Protection Act ("Infektionsschutzgesetz"). Persons tested positive for SARS-CoV-2 will be obliged to follow the instructions of the local health authorities.

The local health authorities will be responsible for deciding whether or not the daycare centre attended by the SARS-CoV-2 positive child / where the SARS-CoV-2 positive childcare worker works can remain open.

Re-admittance to the daycare centre will be subject to the instructions issued by the local health authorities.

Household members of participants tested positive for SARS-CoV-2 will be tested according to the instructions of the local health authorities. Serology for SARS-Cov-2 antibodies will be carried out 2 weeks after the end of the quarantine period imposed by the local health authorities if written informed consent was obtained for venous blood sampling within the study.

Unless the local health authorities issue instructions to the contrary, the daycare unit (the entire daycare centre or the relevant group) of the SARS-CoV-2 positive child/childcare worker will be tested for SARS-CoV-2 twice a week for a duration of 2 weeks after the date of diagnosis.

#### 4.3.2 Psychosocial Dimension (questionnaire)

Successful implementation of the intended monitoring measures is highly dependent upon the acceptance by parents, children and daycare centers. As yet, no systematic data is available on the extent of willingness to participate in such preventive measures in the SARS-CoV-2 pandemic or on the acceptability of such measures. Analysis of the feasibility of the four monitoring protocols must therefore be accompanied by both quantitative and qualitative research elements involving all persons concerned. The feasibility study will furthermore offer the opportunity to gather data on factors potentially affecting acceptance of the monitoring measures in order to identify potential targets for accompanying interventions aimed at increasing the level of acceptance.

The Wü-KiTa-CoV study will gather questionnaire-based data on the acceptance of the respective monitoring protocol by parents/guardians, children and childcare workers three times during the study period (at the beginning of the study period and during and after the implementation of the measures). Families with more than one participating child will be asked to fill in separate questionnaires per child. The following potential predictors of acceptance will be examined:

- a) sociodemographic factors (e.g. educational level, place of residence, number and ages of children)
  - b) Expectations and opinions of the parent/guardian regarding the measures to be introduced
  - c) Existence and severity of mental health symptoms (anxiety and depression in particular).
- The assessment of mental health symptoms will be based on questionnaires using validated psychometric instruments/scores (e.g. PHQ4, EQ-5D and a short form of CBCL) and a sociodemographic question battery which is also used within the CORONA HEALTH APP Study in cooperation with the Robert-Koch Institute (PI: [name], Co-PI: [name]).

Qualitative interviews will be conducted in a sample of parents/guardians and with childcare workers from all daycare centers in order to gain further insight into the study participants' expectations, wishes and reservations concerning the measures to be introduced. Follow-up interviews at the end of the intervention programme will seek to establish reasons for acceptance or lack of acceptance in order to identify potential barriers and obstacles to practical implementation and develop ways of minimising these. The same interview partners as in the initial interviews will be invited to these follow-up interviews. Only in the event of their non-participation will new interview partners be recruited. The selection process for inviting participants to qualitative interviews will take sociodemographic characteristics into account as far as possible in order to maximise variation of characteristics with respect to age, sex, educational level, family status and place of residence (purposive sampling). The reasoning for the use of this sampling method is the assumption that the aforementioned sociodemographic characteristics will influence the aspects / topics identified in the interviews.

The interviews will use semi-structured interview guidelines and will be carried out by telephone. Duration of the interviews is estimated at 30 minutes. The interviews will be recorded on tape and subsequently be pseudonymised and transcribed. Coding and analysis of the qualitative interview data will follow a content analysis approach with a mixture of deductive and inductive methods according to Kuckartz using the MAXQDA software. The data obtained in the interviews will be analysed in parallel with the process of conducting interviews, and recruitment of further participants will end once no additional aspects/topics are to be expected (data saturation).

Children aged three years and above will be interviewed within the daycare centre three times during the study period by members of the study team who will ask the children one question each regarding their experience of the swab sampling, their motivation to have further swabs taken and their perception of their own cooperation.

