#### **Recruitment/ individual course of study**

##### *Initial measurement*

The central study office will provide all participating daycare centers with the information material relevant to the assigned study module, the written participant documents (informed consent forms, initial questionnaire) and sealable envelopes pre-addressed to the central study office to be used by the parents/guardians to return the documents.

The participating daycare centers will collect the envelopes with the informed consent forms and the initial questionnaires returned by the parents/guardians and forward all documents to the study team. The central study office will check and archive the documents, create participant lists per daycare centre and assign a unique participant number to each participant (pseudonymisation).

The data pertaining to the study (initial questionnaire and follow-up questionnaires) will be stored in pseudonymised form in the EDC (Electronic Data Capture) system REDCap®.

The EDC system will be hosted on servers belonging to the University of Würzburg and administered by the University of Würzburg's computing centre. The security policy conforms to the University of Würzburg standard. Access to the stored data will be granted via the EDC system's role and rights management system.

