### **Exploratory Analyses regarding psychosocial effects: Data collection using survey questionnaires related in terms of content to the coronavirus contact tracing app ("Corona-Warn-App") published by the Robert Koch Institute and additional qualitative interviews at the beginning and end of the intervention**

- Parents' satisfaction with the screening measure (weeks 1, 6, 12)
- Parents' sense of security due to the screening measure (weeks 1, 6, 12)
- Children's satisfaction (increase/decrease of anxiety, crying, defensive movements, refusal to attend daycare centre) (weeks 1, 6, 12)
- Subjective stress level caused by screening measure (weeks 1, 6, 12)
- Negative effects of screening measure on family climate (weeks 1, 6, 12)
- Organisation of daily routines affected by screening measure (weeks 1, 6, 12)
- Occurrence of effects personally perceived as negative consequences of the screening measures (e.g. quarantine period following a positive SARS-CoV-2 test) (weeks 1, 6, 12)
- Mental health symptoms according to validated questionnaires (weeks 1, 6, 12)

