## **7.2 Data analysis methods**

The primary endpoints will be estimated as 95% confidence intervals using the Wilson score method. Due to the purely exploratory nature of all analyses and the fact that the four modules will be implemented in separate daycare centers, the significance level will not be adjusted for multiple testing and all analysis results will be interpreted with the necessary caution. The significance level will be set to 5% for all analyses. In a first step, descriptive analyses

(frequency (percent), mean (SD) or median (IQR)) will be reported for all endpoints. The analysis of the secondary endpoints drop out rate, initial rate of consent, acceptance of blood sampling (stratified by childcare workers and parents), proportion of positive serological tests and proportion of positive PCR tests will, in a first step, compare all four groups using test procedures such as the Chi-squared-test, ANOVA or the Kruskal Wallis test as appropriate. Subsequently, pairwise comparisons will be carried out using appropriate post-hoc tests. The rate of acceptance will first be compared between all modules 1 to 3 using the chi-squared test. Analysis of the development of the psychosocial factors over time will be stratified by monitoring module and will use tests for repeated measurements such as the McNemar test, Repeated Measurements ANOVA and the Friedman test. In addition, baseline values and the follow-up values after 12 weeks will be compared between modules using appropriate tests such as the chi-squared test and ANOVA or non-parametric tests followed by post-hoc tests. Potential predictors of the rate of acceptance will be analysed (overall for all modules combined and stratified by module) in univariable analyses using the chi-squared test and, if a sufficient sample size is obtained, additionally using multivariable logistic regression. The analysis of costs, the proportion of absent days and data on the closure of daycare groups will be restricted to descriptive methods. The development of seroprevalence data over time will be reported using descriptive methods, possibly including graphical displays. The results of the children interviews will be reported descriptively using frequencies. If possible, an ICC value (intraclass correlation) for the daycare centers will be calculated as a basis for sample size estimation for a future cluster randomised study. All analyses will be performed in SAS, R or SPSS.

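### Separate questionnaires per child, with no separate parent form, family identifier or one-record-per-parent rule, probably record parent-level psychosocial outcomes more than once in families with several participating children

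*Protocol*

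**What the plan says.** Section 4.3.2 fixes the unit of collection: "Families with more than one participating child will be asked to fill in separate questionnaires per child". The assessments there combine scales that would ordinarily describe an adult respondent with a child behaviour measure: "validated psychometric instruments/scores (e.g. PHQ4, EQ-5D and a short form of CBCL". The three waves are weeks 1, 6 and 12.

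The psychosocial outcomes in section 7.1 include items that belong to the parent or household, among them "Parents' satisfaction with the screening measure (weeks 1, 6, 12", "Parents' sense of security due to the screening measure (weeks 1, 6, 12" and "Negative effects of screening measure on family climate (weeks 1, 6, 12", together with the organisation of daily routines. The mental health outcome, "Mental health symptoms according to validated questionnaires (weeks 1, 6, 12", does not separate adult from child scales. Children's own reactions to the measure are a further outcome in the same list.

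For change over time within a module, section 7.2 "will use tests for repeated measurements such as the McNemar test, Repeated Measurements ANOVA and the Friedman test". Baseline and 12-week values are compared between modules with chi-squared, ANOVA or non-parametric tests, all at 5%. The only clustering mentioned is an intraclass correlation for daycare centres, intended for planning the next study. Section 7.3 puts all participants' data into the main analysis. The identifier in section 6.1 is individual: the study office will "assign a unique participant number to each participant (pseudonymisation". Section 13.3 lists psychosocial questionnaires without dividing them into parent and child parts.

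**The concern.** A parent's sense of security, the family climate or an adult mental health score does not become a second observation because a sibling also takes part. If those items appear on each child's form, one parent enters the data twice or more at each wave. The tests for repeated measurements deal with repeats over time, not with several records from one parent at the same time. The between-module tests assume that every record is independent.

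There are two consequences. Standard errors are too small, so tests reject too often. Means are also pulled towards families with several participating children. What drives that weight is the number of participating children, not family size. Module 3 excludes children under 2, so a family with one child under 2 and an older sibling can return two forms in modules 1, 2 or 4 but only one in module 3. The extra weight can therefore differ between the modules being compared.

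Satisfaction and sense of security are the content of both secondary hypotheses in section 2.2, so this reaches named study questions, though not the primary one.

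**Working it through.** The protocol states no sample size, precision or power for the questionnaire outcomes, so there is no figure to reproduce. The calculation below shows the size of the effect under stated assumptions.

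**Inputs**
- Significance level 5% (section 7.2).
- f, the share of families with two participating children: not given, assumed 0.10 to 0.40.
- rho, the correlation between the two forms from one family: not given, assumed 0.5 to 1.0. For a between-module comparison at one wave this is the correlation of the answers; for change over time it is the correlation of the changes.
- Each questionnaire is counted as one unit: assumed, because the protocol does not state the unit.

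**Formulas**
- Weight of two-child families in a per-questionnaire mean: w = 2f/(1+f).
- Design effect: DEFF = [(1−f) + f(2+2·rho)]/(1+f), which simplifies to 1 + w·rho.
- True two-sided level of a nominal 5% z-test: 2·[1 − Φ(1.96/√DEFF)].

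**Lower end, worked.** With f = 0.10 and rho = 0.5, w = 0.20/1.10 = 0.182 and DEFF = (0.90 + 0.30)/1.10 = 1.09. Then √DEFF = 1.044, 1.96/1.044 = 1.88, and the true level is 6.1%.

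**Upper end, worked.** With f = 0.40 and rho = 1.0, w = 0.80/1.40 = 0.571 and DEFF = (0.60 + 1.60)/1.40 = 1.57. Then √DEFF = 1.254, 1.96/1.254 = 1.56, and the true level is 11.8%.

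| f | Weight of two-child families | DEFF, rho 0.5 | DEFF, rho 1.0 | True level, rho 0.5 | True level, rho 1.0 |
|---|---|---|---|---|---|
| 10% | 18.2% | 1.09 | 1.18 | 6.1% | 7.1% |
| 20% | 33.3% | 1.17 | 1.33 | 7.0% | 9.0% |
| 30% | 46.2% | 1.23 | 1.46 | 7.7% | 10.5% |
| 40% | 57.1% | 1.29 | 1.57 | 8.4% | 11.8% |

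**Standard errors.** The understatement is 1 − 1/√DEFF, from 1 − 1/1.044 = 4% to 1 − 1/1.254 = 20%.

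**Shift in the mean.** If one-child and two-child families differ by 10 points on an outcome, the per-questionnaire mean differs from the per-family mean by 10·(w − f): 10·(0.182 − 0.10) = 0.8 points at f = 0.10, and 10·(0.571 − 0.40) = 1.7 points at f = 0.40.

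**After the fix.** With one parent record per family, each family has weight 1 and the design effect from duplication is 1.0, so the 5% level holds with respect to this source of dependence.

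**The case against.** The strongest reply is that much of the harm is inferred. A reader might conclude that the plan makes the same parent repeat the whole questionnaire for each child and then analyses every form as a separate subject. The protocol says none of these three things. Section 4.3.2 asks for separate forms per child, but not that adult items recur on the second form or that one parent completes both. Section 7.2 names types of test without a unit of analysis. The instruments are not shown and may already branch, and section 8 refers to a statistical analysis plan that could set one record per family. This stands, and it is why the figures above are conditional.

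Per-child forms also have a proper purpose: children's reactions and the short CBCL need them. Satisfaction with sampling, or stress caused by it, may genuinely differ between a sibling who tolerates swabs and one who does not. This stands too, and is why rho is taken down to 0.5.

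A reader might also infer that the extra forms will reduce response at weeks 6 and 12. That is plausible, but nothing in the protocol documents it. Finally, section 7.2 calls all analyses exploratory and promises cautious interpretation, and neither the primary endpoint nor the precondition for the subsequent study uses these outcomes.

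What the reply does not remove is that per-child collection is a stated rule, not a detail left for later. An analysis rule by family needs a link between siblings. The protocol gives each participant an individual pseudonym and describes no family identifier. The de-identification list in sections 6.2 and 8 might allow siblings to be linked, but that use is not described.

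**Conclusion.** The point holds as a cheap improvement to secondary and exploratory outcomes. The protocol sets collection per child, lists outcomes that belong to the parent or household, and provides neither a separate parent form nor a family link nor a rule for repeated parent answers. On the natural reading, those answers are recorded more than once for families with several participating children.

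The size depends on three assumptions that the protocol does not settle: each questionnaire is analysed as a unit, 10-40% of families have two participating children, and the correlation between their forms is 0.5-1.0. Under these, the design effect is about 1.1-1.6 and the true level of a nominal 5% test about 6-12%. If the forms already separate parent from child items, or the analysis already uses one parent record per family, the inflation for parent-level outcomes disappears and a clarifying sentence is enough. The primary acceptance endpoint and its success thresholds are unaffected.

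**What to change.** - **Section 4.3.2:** have items that describe the parent or household (sense of security, family climate, daily routines, adult mental health scales, general satisfaction) completed once per responding parent at each wave. Have child-specific items completed once per child: the child's reactions, the short CBCL, and any satisfaction or stress item tied to a particular child's sampling.
- **Section 6.1:** add a pseudonymised family identifier that links siblings and their responding parent.
- **Sections 7.1 and 7.2:** state that parent-level outcomes are analysed with one record per parent or household. Where siblings contribute child-level records, account for family, for example with a family random effect or family-robust standard errors.
- **If the forms are already fixed:** use one parent block per household and wave, chosen by a pre-specified rule such as the first completed.

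The cost is a small change to questionnaire branching, one extra variable, and a smaller nominal number of records for parent outcomes. Families with several participating children would have less to complete.
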